### Cost-effectiveness analysis

The aim of this sub-study is to estimate the value for money of implementing IeDA compared to current practice (implementing standard IMCI, based on the paper-based IMCI protocol) in the diagnosis of under-5 children in primary healthcare centres in Burkina Faso. The CEA, embedded within the IeDA stepped-wedge trial, will estimate both the cost per consultation and the incremental cost per child correctly managed associated with delivering IeDA compared to delivering standard IMCI. The perspective for the CEA is that of the healthcare provider, i.e. the MoH. For both standard IMCI and IeDA, costing will be undertaken using a micro-costing approach [32]. For each of the two interventions, the main components of the cost per consultation are as follows: (i) programme costs, i.e. costs associated with the implementation of the intervention that are incurred at the administrative level outside the point of delivery of healthcare, and (ii) patient costs or costs associated with the implementation of the intervention which are incurred at the point of delivery of healthcare [33]. To obtain an adequate estimate of the cost per consultation for each of the two interventions, programme costs will be allocated to patient costs using established cost allocation procedures [32].

The cost per consultation of IeDA and standard IMCI will be estimated using an observational before-and-after study design in the district of Ouahigouya, one of the districts included in the stepped-wedge trial. In this district, the costs per consultation of standard IMCI will be estimated during the 6-month period prior to IeDA implementation. The cost per consultation for IeDA will be estimated during the 6-month period after IeDA implementation.

For both arms, all resource consumption affecting programme costs at health centre and district level will be measured prospectively using surveys. This data will be supplemented with data from health centre and district accounts. All resource consumption affecting programme costs at national level will be measured retrospectively via interviews with agents who have participated in the implementation of both interventions (mostly MoH officers and, in the case of IeDA, also TdH coordinators). Resource consumption affecting patient costs will be measured using data recorded in the REC for every consultation in the ten Ouahigouya health centres selected for the stepped-wedge trial which is monitored in the period between 6 months before and 6 months after IeDA implementation. For each of the two interventions, the number of consultations monitored in the Ouahigouya health centres during this period is scheduled to be 80. Data collected in the REC for each patient consultation includes (i) duration of the consultation and (ii) medications prescribed in the consultation. An additional form will be added to the REC to measure consumables used during each patient consultation. To minimise bias in the measurement of resource consumption due to seasonal effects on healthcare delivery, data on resource consumption from all the consultations monitored in the stepped-wedge trial (whether standard IMCI or IeDA) 3 months before and 3 months after IeDA implementation in Ouahigouya will be used in the estimation of patient costs. Once resource consumption is measured, costs will be calculated using unit prices for each resource consumed. Depending on the specific type of resource, unit prices will be obtained from MoH databases, MoH price lists or supplier catalogues.

Regression analysis will be used to estimate the mean difference in costs per consultation between IeDA and standard IMCI. Cost-effectiveness modelling will be used to assess the incremental cost-effectiveness of IeDA versus standard IMCI.

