#### Data collection

As outcome measures, the trial is assessing the adherence to IMCI guidelines and the correctness of the illness classification, prescription, referral (if necessary) and counselling.

Each selected CSPS is visited for 1 or 2 days at each ‘step’ of the trial by a team of two staff from the evaluation team. One member of staff observes all under-5 children consultations performed by the local health workers while the other reassesses children after their consultation with the local health worker. Our teams notify the head of the health centre the afternoon of the day before our visit.

The first member of the evaluation team records information regarding each consultation in a detailed observation form. Three observation forms were designed, one per age category defined by the IMCI guidelines (i.e. 0–7 days, 7 days–2 months, 2 months–5 years) and pre-tested to include all questions or tasks that a healthcare worker should perform when following the IMCI guidelines. Each observation form is divided into sections corresponding to the different sections in the IMCI protocol for each age category. For instance, the observation form to observe consultations of children from 2 months to 5 years old includes sections for the assessment of danger signs: cough or fast/difficult breathing, diarrhoea, fever, ear problems, anaemia, nutritional status, HIV, immunisation and vitamin A uptake, referral, treatment and counselling. Observations are passive, and the observer never intervenes during the consultation. Information recorded in the observation form also includes whether the nurse referred to the IMCI chart booklet during the consultation or used the REC (if the district benefited from the intervention), as would be expected if IMCI was being implemented correctly. If the health centre has more than one nurse conducting child consultations, the observer follows the first child who is called for consultation.

Following observation of a consultation, the second member of the evaluation team, expert in IMCI, re-assesses the child independently using the REC to provide a ‘gold standard’ against which to compare local health workers’ classifications and treatment decisions. In case of discrepancies between the health worker and the IMCI expert, the final management decision is determined following discussions between the two of them.

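### Patient costs of standard IMCI are to be taken from the electronic register, which health workers in Ouahigouya do not have before IeDA

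*Protocol article*

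**What the plan says.** All references are to the protocol article.

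**Source of patient costs (Cost-effectiveness analysis).** "Resource consumption affecting patient costs will be measured using data recorded in the REC for every consultation in the ten Ouahigouya health centres", "which is monitored in the period between 6 months before and 6 months after IeDA implementation". The items are named: "Data collected in the REC for each patient consultation includes (i) duration of the consultation and (ii) medications prescribed in the consultation". Consumables follow the same route: "An additional form will be added to the REC to measure consumables used during each patient consultation". The planned volume is given too: "For each of the two interventions, the number of consultations monitored in the Ouahigouya health centres during this period is scheduled to be 80". Surveys, accounts and interviews are assigned to programme costs, and price lists and catalogues supply unit prices only. No other source of patient-level resource use is named.

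**Comparator (Cost-effectiveness analysis).** Current practice is described as "implementing standard IMCI, based on the paper-based IMCI protocol", and its cost per consultation is estimated in the 6 months before IeDA starts in Ouahigouya.

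**Who uses the REC (Data collection).** The observer notes whether the nurse consulted the chart booklet or "used the REC (if the district benefited from the intervention". The second team member, an IMCI expert, then re-assesses the child with the REC as the gold standard. The health worker's own consultation is recorded on the observation form.

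**The concern.** The section names one instrument for both periods, but before IeDA the health worker whose consultation is to be costed does not work with it. A pre-intervention REC record, if one exists, would describe a different consultation: one by an expert, guided by the REC, on a child who has just been seen.

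Duration, medicines and consumables make up the patient-cost part of the cost per consultation. They enter the regression for the mean cost difference and then the incremental cost per child correctly managed. The effectiveness side of that ratio describes what health workers do. If the comparator's patient cost describes what the expert does, numerator and denominator no longer refer to the same care.

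**Working it through.** **1. Could nurses in Ouahigouya have had the REC before IeDA?**
- The section on the Electronic Register and the IeDA intervention lists rolling out the improved REC as the first of the five IeDA components, delivered at district level.
- The section on the evaluation methods excludes the three districts in which the REC was piloted.
- The Cost-effectiveness analysis section says that Ouahigouya is a stepped-wedge district, so it is not one of those three.
- The Data collection section expects nurses to use the REC only where the district has the intervention.

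The article therefore describes no nurse use of the REC in the 6 months before IeDA.

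**2. What REC use is described in the control phase?** Only the expert's re-assessment after the consultation.

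**3. The figure of 80 per intervention.** The article does not derive it. It fits 10 centres × 1 visit × 8 children = 80, or 10 × 2 × 4 = 80, so it can be neither confirmed nor refuted. On the text as written, 0 of the 80 standard-IMCI consultations have a described health-worker REC record, whereas all 80 IeDA consultations could have one.

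**4. What would be estimated?** Let P0 and P1 be the mean patient cost of the health worker's consultation before and after IeDA, and E0 and E1 that of the expert's REC-guided re-assessment. The target is P1 − P0.

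| Record used before | Record used after | Estimate | Error against P1 − P0 |
|---|---|---|---|
| none | nurse's REC | not estimable | – |
| expert's REC | nurse's REC | P1 − E0 | P0 − E0 |
| expert's REC | expert's REC | E1 − E0 | (E1 − E0) − (P1 − P0) |

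In the second row the sign depends on whether the expert's re-assessment costs more or less than the nurse's paper consultation. A complete, guided assessment may take longer. An experienced assessor (at least 5 years of IMCI, per Data collection) repeating an assessment may be quicker. Prescribing also differs: the Background cites about 30 % correct prescription of an antibiotic for suspected pneumonia or ORS for diarrhoea in a 2013 evaluation. An expert's prescriptions would not represent that practice, but whether they cost more or less is not known. The article gives no durations, drug costs or consumable costs, so no size can be computed.

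**5. How far does the error carry?** With ΔC = Δ(programme cost) + Δ(patient cost) and ICER = ΔC / ΔE, an error b in the patient-cost term shifts the ICER by b / ΔE. The programme-cost term comes from surveys, accounts and interviews and is untouched.

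**6. Does the seasonal supplement help?** It adds consultations monitored in the stepped-wedge trial in the 3 months before and after IeDA starts in Ouahigouya. Its standard-IMCI consultations come from districts still in the control phase, where nurses also lack the REC, and no other instrument is named. The same problem recurs.

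**The case against.** The strongest reply is that the data are limited to monitored consultations, at which the evaluation team is present, and that a consumables form is being added to the REC. The team could therefore enter the observed nurse's consultation on REC-based forms. A condensed article commonly leaves such operational detail to the full protocol, and this is one component of an economic sub-study.

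Part of this stands. That third reading is possible and would remove the problem. But the article does not state it, and the Data collection section assigns the recording of the nurse's consultation to the observation form and the REC to the expert. Nor is this merely absent detail: the article does name a source, and the comparator as described does not have it.

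Two further points stand in full. Cost per consultation has a programme component that does not depend on the REC. And the observation form is not shown, so it may already hold times or consumables; the article mentions a treatment section but neither of those items.

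**Conclusion.** The Cost-effectiveness analysis and Data collection sections contradict each other on the source of comparator patient costs. As written, the patient-cost part of the standard-IMCI cost per consultation is either unavailable or that of an expert's REC-guided repeat consultation. The incremental patient cost and the incremental cost per child correctly managed would then be biased, by an amount and possibly in a direction that cannot be computed from the article. The standard-IMCI consultations in the seasonal supplement are affected in the same way. Programme costs, the co-primary outcomes and the trial analysis are not.

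A reader might infer more: that the REC would be compared with the REC, so that the cost difference vanishes by construction. The documents do not support this. It would need the expert's record to be used in both periods and expert practice to stay unchanged between them. If the nurse's REC record is used after IeDA, the contrast is nurse against expert, who differ in experience and task, and nothing forces it to zero. Even a zero patient-cost difference would leave the programme-cost difference in place.

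The verdict rests on the article as it stands, and on evaluators not entering the nurse's consultation in a REC-based form.

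**What to change.** Reconcile the Data collection and Cost-effectiveness analysis sections as follows:

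- Take duration, medicines and consumables of the health worker's own consultation from the direct-observation record, for standard IMCI and IeDA alike, on the same instrument in both periods.
- Add start time, end time and consumables used to the observation form if it does not already hold them.
- State that the expert's re-assessment record is not used for costing.
- Apply the same rule to consultations from other districts that enter the seasonal supplement.

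The cost is a few extra fields for an observer who already attends the consultation and completes a form; no added staff or visits are needed. The change has to be in place before the control-phase consultations used for costing are observed, because times and consumables that were not recorded then cannot be recovered later.

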### Realist evaluation

For Pawson and Tilley [34], issues of context and mechanism are crucial elements to consider in any realist evaluation as they help to explain ‘what works, for whom and in what circumstances’. For these authors, ‘what works’ is not of itself a helpful question as: ‘programs work (have successful “outcomes”) only insofar as they introduce the appropriate ideas and opportunities (“mechanisms”) to groups in the appropriate social and cultural conditions (“contexts”)’. Focusing on the realist dimensions enables us to examine the particular significance of ‘mechanism’ and ‘context’ more closely.

We will use longitudinal research, using a case study design [35], to enable us to understand the impact of key features or mechanisms for IeDA users and the context in which adherence to protocols is achieved (or not) over time.

In the case studies, the task of the research team will be to identify different context and mechanism configurations. These case studies will be purposively selected in relation to the performance of the health centre (in terms of adherence to the protocol) and the capacity of health centre staff to reflect on their experience. Informed by data from the stepped-wedge trial (high-performing and low-performing health centres), new cases identified from the list of health centres randomly selected in the trial will be added to our purposive sample. Four intervention health centres with high performance (positive cases) and four intervention health centres (deviant cases) with low performance will be selected.

Given the broad scope of the study and a desire to capture how IeDA works in situ, we will use a combination of methods:Non-participant and participant observation of nursing and multi-disciplinary activities related to the use of IeDA (e.g. supervision from district managers, relation with pharmacist)Post-observation interviews guided by issues arising from observationsSocial network analysis to explore whether the nature of relationships between the actors of the health system will change [36, 37]Key stakeholder interviews exploring views in general about the use, influences on use and impact of IeDA. We will record the interviews and code and analyse them using the software NVivoInterviews with patients about their experience of IeDASurvey questionnaire administered to REC users to understand their experience using the tool and perceptions on the benefits or constraints of RECReview of relevant documentation (e.g. reports, statistics)Field notes written during and after each visit

In the realist evaluation sub-study, the analysis will consist of identifying patterns and variables in one case study [38] through a ‘pattern matching’ process [39] and verifying the presence of the same pattern in other case studies where it was expected to obtain the same pattern, what Yin called ‘theoretical replication’ [38, p. 116]. Cross comparisons will also be made with deviant cases where other patterns are expected to be found for predicted reasons.

To enable comparisons, data analysed in the trial on the level of adherence, resource availability and health facility size and compared across areas and health centres will be used to identity well-performing heath centres and poorly performing health centres. This will allow qualitative cross-case analysis taking into account similarities and differences between health centres.

## Discussion

### Interconnected sub-studies

With the IeDA study, we aim for a holistic evaluation in which outcome, process and cost data are integrated in the analysis of the findings to maximise our capacity to understand the effect of the introduction of a complex intervention into a specific context.

In integrating outcome, process and cost data, we focus on three key questions: (i) How does the effectiveness and the cost of the intervention vary by type of health worker and type of health centre? (ii) What is the impact of changes in the content, coverage and quality of the IeDA intervention on adherence and cost-effectiveness? (iii) What mechanisms of change (including costs) might explain the relationship between the IeDA intervention and adherence?

To explore whether more intensive implementation of the IeDA intervention can generate better adherence outcomes, data collected on implementation parameters (e.g. fidelity and dose) will be used to categorise and rank health centres. We will calculate the correlation between outcome and the fidelity and dose of the IeDA intervention.

In addition, process and cost data will be integrated into the trial analysis to identify new hypotheses on factors influencing the performance of health centres. Two factors that may play an important role in performance are (1) the characteristics of health workers (e.g. their experience in IMCI, the time allocated to each consultation) and (2) the characteristics of health centres (e.g. team structure, leadership, resources available).

### Ethics

The Ethics Committee of the Ministry of Health of Burkina Faso and the Ethics Review Committee at the London School of Hygiene & Tropical Medicine have approved the trial. Risks and burdens to the patients and the nurse as a consequence of the study are minimal.

Every nurse at the health centre level who will be observed will be informed about the study and the procedures and written consent will be requested. Carers of children will give written informed consent to provide authorisation for one of the researchers to observe the consultation conducted by the nurse and for the other researcher to conduct a repeat consultation.

An information sheet in the local language will be read to all participants (carers who accompany children, nurses, MoH Officials, NGO and United Nations Officers). Participants will be encouraged to ask questions about the research. If consent is given, they will be asked to sign either their name or, if unable to do so, provide their verbal assent and print their thumb print, on the attached consent form.
